### Methods: Assignment of interventions

#### Allocation.

**Sequence generation:** The random sequence, with a 1:1 allocation of participants will be generated using a computer-generated random number in permuted blocks produced with an external website.

**Concealment mechanism:** Sealed opaque envelopes will be used to conceal the protocol order allocation.

**Implementation:** One of the coauthors (*HBS* in the authors’ list) will generate the random sequence. The principal investigator (*SS* in the authors’ list) will enroll participants and randomly assign them to one of the study groups.

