### Recruitment

To recruit participants for the trial, a comprehensive digital survey will be distributed to office workers to identify individuals experiencing NP from September 1 to October 30, 2025. The survey clearly explains the trial and its objectives and expresses that all information will be analyzed with strict respect to anonymity, confidentiality, and medical secrecy. By ticking a checkbox, individuals will express their voluntary commitment to join the study, and will have access to questions identifying general information (***e.g.,*** age, sex, comorbidities, work seniority, average number of daily hours spent in front of computer); the existence of NP, duration of symptoms, pain intensity, which will be evaluated via a pain intensity number rating scale (PI-NRS), medication (***e.g.,*** pain killers, physiotherapy). Individuals identified as potentially suffering from this condition will subsequently be invited to undergo a thorough physical examination by a specialist in the field (*SS* in the authors’ list) to confirm the diagnosis.

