### Informed consent

One researcher (*SS* in the authors’ list) will obtain written informed consents from all eligible participants before allocation. Participants will be clearly informed about the study aims and potential benefits, and that they will be free to withdraw the study at any point with no need to give any specific reason for that. They will be asked if they agree to the use of their data. This trial does not involve collecting biological specimens for storage.

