#### Blinding.

One of the coauthors (*AC* in the authors’ list) who is blinded to the treatment arm will analyze data. The study principal investigator, in charge of explaining and delivering interventions (*SS* in the authors’ list), and the participants will not be blinded to the group allocation.

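### One unblinded investigator examines, enrols, assigns from permuted blocks and delivers both interventions; if assignment is sequential, sealed envelopes do not stop allocations being partly predicted

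*Protocol article*

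**What the plan says.** The relevant roles are spread over several sections of the protocol article. Identical author initials show that they belong to one person, the principal investigator:

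- **Recruitment:** workers whose survey answers suggest neck pain are "invited to undergo a thorough physical examination by a specialist in the field", who confirms the diagnosis.
- **Informed consent:** the same person "will obtain written informed consents from all eligible participants before allocation".
- **Allocation, Implementation:** the same person "will enroll participants and randomly assign them to one of the study groups".
- **Blinding:** the same person explains and delivers the interventions, "and the participants will not be blinded to the group allocation". Only the data analyst is blinded.

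On the sequence itself, Allocation specifies a 1:1 ratio and a "computer-generated random number in permuted blocks produced with an external website". A different coauthor "will generate the random sequence". Concealment reads: "Sealed opaque envelopes will be used to conceal the protocol order allocation". The article does not say who holds and opens the envelopes, or whether everyone is enrolled before the first one is opened.

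**The concern.** Concealment has two parts: nobody who decides on entry may see the next assignment, and nobody who decides on entry may be able to infer it. Envelopes and a separate sequence generator serve the first part. They do not serve the second when the person deciding on entry also learns every earlier assignment, because a 1:1 permuted block forces the arms back to balance.

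The examination leaves room for judgement. The eligibility criteria exclude specific causes, radiculopathy and myelopathy. A worker on the borderline could be accepted, declined or scheduled later according to the arm expected next. The planned difference is only 0.58 PI-NRS points, pain is self-reported by unblinded participants, and the planned adjustment for baseline imbalance cannot reach prognosis or motivation that was not measured.

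This is a point about a stated division of roles. It is not a complaint that the block size is missing, which is normally withheld on purpose.

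**Working it through.** **Inputs.** From Allocation: 1:1 ratio, permuted blocks. From Sample size: 50 participants (44/0.9 = 48.9, planned as 25 per group). The article gives no figure for predictability, so there is none to reproduce. Block size is not stated and is taken as an assumption over the range 2 to 10. Sequential assignment is also an assumption.

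**Rule.** The enroller keeps a tally and always guesses the arm that is behind, tossing a coin when the arms are level.

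**Block of 4 by hand.** The first allocation is guessed with probability 1/2. The second is guessed with probability 2/3, since two of the three remaining cards are for the other arm. Before the third, the arms are level with probability 2/3 (guess right 1/2) or one arm is full with probability 1/3 (guess right 1): 2/3 × 1/2 + 1/3 × 1 = 2/3. The fourth is always known.

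(1/2 + 2/3 + 2/3 + 1)/4 = 0.708 guessed correctly.

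Known with certainty: the third with probability 1/3 and the fourth always, so (1/3 + 1)/4 = 0.333.

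**General form.** For a complete block of size 2m:

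- expected share guessed correctly = [m − 1/2 + 2^(2m−1)/C(2m, m)]/(2m)
- share known with certainty = 1/(m + 1)

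For m = 2 the first gives (1.5 + 8/6)/4 = 0.708, as above. For m = 5 it gives (4.5 + 512/252)/10 = 0.653.

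| Block size | Correct, complete blocks | Certain, complete blocks | Correct, 50 allocations | Certain, 50 allocations |
|---|---|---|---|---|
| 2 | 0.750 | 0.500 | 75% | 50% |
| 4 | 0.708 | 0.333 | 70% | 32% |
| 6 | 0.683 | 0.250 | 68% | 24% |
| 8 | 0.666 | 0.200 | 66% | 19% |
| 10 | 0.653 | 0.167 | 65% | 17% |

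The last two columns come from 10,000 simulated sequences of 50. They fall slightly below the complete-block values for blocks of 4, 6 and 8 because 50 is not a multiple of these sizes.

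**What each column needs.** The certain share needs a fixed block size that the enroller knows or has worked out. The guess rate needs only the running tally: simulating blocks of 4 with the block boundaries hidden again gave 70%.

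**Alternatives, simulated the same way.**

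- Block size varying at random between 4 and 6, boundaries unknown: 69% correct.
- Varying among 4, 6 and 8: 68% correct.
- Whole list allocated in one step after enrolment has closed: 50%, none certain.

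Varying the block size therefore removes most of the certainty but little of the guessing advantage.

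**The case against.** The strongest objection is that the article never says assignment is sequential. Consent is taken from all eligible participants before allocation, and the survey window is closed (1 September to 30 October 2025). Both fit a batch allocation, in which nothing could be steered. This stands as a condition on the point. But the consent sentence can equally mean that each person consents before his or her own allocation, and nothing requires enrolment to finish first.

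Second, prediction comes from knowing past assignments, which the investigator learns by delivering the interventions, and not from opening the envelope. This is correct. Moving the assigning task to someone else while starts stay staggered would prevent tampering with envelopes but would leave the tally.

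Third, there is little room to reject anyone. The Introduction cites one-year prevalences of 33% to 69%; among 70 workers that is 70 × 0.33 = 23 to 70 × 0.69 = 48 with any neck pain, fewer than the 50 wanted. If those rates apply, outright refusal is unlikely, although the order of entry can still be changed. Pain and duration are also first captured by digital survey, outcomes are entered digitally by participants, the analyst is blinded and baseline imbalance is adjusted for. These are real but partial protections.

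A reader might go further and infer a bias of a given size. If workers enrolled when the app is expected differed in prognosis by δ points from those enrolled when paper is expected, full steering would give a bias of δ × (2p − 1). For blocks of 4 the factor is 2 × 0.708 − 1 = 0.417. With δ from 0 to 1 point the bias runs from 0 to 0.42 points, or 0% to 72% of 0.58. No value of δ has a source in the article, and the formula assumes steering at every informative position. It shows what would have to be assumed and is not an estimate.

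**Conclusion.** The point holds as a conditional risk. The article gives one unblinded person the examination, consent, enrolment, assignment and delivery, with permuted blocks. If assignment is sequential, about 65% to 75% of allocations could be guessed correctly for fixed blocks of 10 down to 2, and about 68% to 69% for varying blocks, against 50% by chance. Sealed envelopes and a separate sequence generator do not change this.

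The document does not support three stronger readings. It does not show that the comparison will be biased, because sequential assignment is not stated and steering is only a possibility. It does not show that a particular number of the 50 allocations will be known in advance, because that needs a known fixed block size. It does not allow the bias to be expressed as a share of the planned difference. The role assignment should be changed because the change is cheap; it is not a fatal flaw.

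**What to change.** Change the Implementation text under Allocation as follows:

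1. For everyone recruited through the closed survey window, examination, consent and baseline PI-NRS, NDI and SF-12 are completed and locked before any allocation.
2. The coauthor who generates the sequence then allocates the whole list of eligible study IDs in one step.
3. The principal investigator no longer assigns participants or handles envelopes.

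This removes prediction as a route to steering, because no entry decision remains open when the first assignment becomes known. It uses a coauthor already named for the sequence and changes neither arms, outcomes nor sample size. The cost is that workers screened early wait until the window closes.

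If starts must be staggered, that coauthor should hold the list and release each assignment only after enrolment is irrevocable, with varying block sizes not disclosed to the principal investigator. This reduces certainty and prevents tampering, but correct guesses stay near 68% to 69%. The protocol should then describe it as a partial safeguard.

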#### Blinding.

One of the coauthors (*AC* in the authors’ list) who is blinded to the treatment arm will analyze data. The study principal investigator, in charge of explaining and delivering interventions (*SS* in the authors’ list), and the participants will not be blinded to the group allocation.

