### Trial design

A single blinded two-armed randomized controlled trial will be conducted. Participants will be assigned randomly to either the interventional group (IG), utilizing the smartphone app, or the control group (CG).

Fig 1 details the schedule of enrolment (Recommendation for interventional Trials).

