### Description of the developed smartphone app

The smartphone app is designed using Android Studio and Flutter. It integrates advanced features, including an intuitive interface and an easy-to-use solution for all users (***i.e.,*** patients and healthcare professionals). Each participant in the IG will receive a code and password to log into the app and to register some general information such as age and sex. All assigned authentications will be recorded in a database created by Firebase. The app features several integrated modules:

(i) Basic information about NP and ergonomic advice on proper neck position during daily work,(ii) Series of evaluation questions including pain assessment (PI-NRS) and the impact of NP on participant’s daily functioning,(iii) Appropriate sets of exercises with videos and instructions,(iv) Daily reminder feature to prompt users to engage in their prescribed exercises consistently, and(v) Evaluation report providing feedback on user’s state and tracking their adherence.

To record participants’ engagement with the program, adherence will be monitored using a user activation tracking system assessing the frequency and duration of app use. The application is linked to the Cloud and Firebase tool enabling the therapist to visualize participants’ results in a graphical form. Exercises included are automatically adapted at each use of the app according to the participant’s condition and evolution. Indeed, the app is designed to analyze the data collected before each use from the evaluation questions based on an AI algorithm and to provide personalized exercise recommendations. To monitor and ensure participant engagement, app usage analytics will be utilized to track interaction patterns and identify any drop-offs in usage. Participants will also have access to technical support to troubleshoot any issues with the app, ensuring minimal disruption. Additionally, scheduled check-ins with participants will be conducted to address potential barriers to engagement and encourage continued adherence to the intervention protocol.

The diagram block (Fig 3) illustrates the app, which is composed of distinct therapist and participant interfaces.

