### Outcomes

The main outcome measure is pain intensity, evaluated according to the PI-NRS [28–30]. The latter is a commonly used tool to measure a person’s pain intensity [28–30]. It is simple, quick, and widely accepted in both clinical and research settings [28–30]. Participants will be asked to indicate their current level of pain on a line from 0 (no pain) to 10 (unbearable pain) [28–30].

Secondary outcome measures are function (***i.e.,*** neck disability index (NDI)), QoL and participants’ adherence to self-exercises. The French validated version of the NDI will be used to assess the impact of NP on individual’s daily functioning [31]. The scale consists of a set of questions addressing various aspects of NP and its influence on activities such as personal care, lifting, reading, working, and recreation. Participants will be asked to rate their level of disability or limitation on a scale for each activity. The total score provides a quantitative measure of the perceived disability associated with NP, with higher scores indicating greater impairment [32]. The French validated version of the short form 12 (SF-12) will be used to measure health-related QoL. The SF-12 is a shorter version of the short form 36, which assesses an individual’s physical and mental well-being. The SF-12 is often utilized in health research, clinical practice, and population health studies [33,34]. Adherence will be measured via two methods. First, it will be evaluated using a frequency-based response scale (***i.e.,*** never, seldom, often, almost always, and always) adapted from the adherence scale of Sluijs et al. [35]. Adherence will then be treated as a dichotomous variable (***i.e.,*** adherent or not adherent), participants who will report “always” or “almost always” will be considered adherent [21]. Second, adherence will be measured based on the frequency of exercise sessions completed. Participants who engage in exercises three or more times per week will be categorized as demonstrating “full adherence” whereas those who exercise twice per week or less will be considered to exhibit “partial adherence”. These combined methods ensure a comprehensive evaluation of adherence, capturing both self-reported behavior and objective frequency of exercise.

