### Methods: Data collection, management, and analysis

#### Plans for assessment and collection of outcomes.

Evaluations will be made at baseline, at the end of the intervention period (fourth week), and at 12 weeks follow up. All evaluations will be performed digitally through a questionnaire where participants will be invited to self-report their level of pain (PI-NRS), their functional disability (NDI), their QoL (SF-12), and to rate their adherence to exercises. At the baseline education session, questionnaires and evaluation tools will be explained to participants to resolve any doubt while answering.

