### Statistical methods

All data will be analyzed using SPSS version 23. The Shapiro-Wilk test will evaluate the normal distribution of quantitative data. If the distribution will be normal and the variances are equal, the quantitative data will be reported as mean ± standard deviation, and 95% confidence interval. Otherwise, data will be expressed as median (interquartile range). Categorical data will be expressed in percentage frequencies. The between-group differences in the mean changes of the outcome measures (PI-NRS, NDI, SF-12, adherence) after intervention will be calculated using repeated measures mixed models with participants from the IG as random effect, and group (IG or CG) and time (baseline, four weeks, and 12 weeks) as fixed effects, and with adjustments for baseline imbalance. The Spearman rank test or Pearson product-moment correlation coefficient analysis will be used to analyze the associations between clinical data and mean changes in the outcome measures. Two-sided statistical significance is set at a p value < 0.05.

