### Oversight and monitoring

#### Composition of the coordinating center and trial steering committee.

The lead researcher (*SS* in the authors’ list) responsible for the study’s design will supervise the trial and manage the project as a whole. As the trial progresses, any necessary corrections will be addressed through decisions made by the entire committee (all authors).

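### The single-blind label covers only the analyst, not the participants who rate the primary outcome, and the planned random effect for one arm contradicts even that blinding

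*Protocol article*

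**What the plan says.** - **Label.** Trial design: "A single blinded two-armed randomized controlled trial will be conducted".
- **Who is blinded.** The Blinding section names one person, a coauthor "who is blinded to the treatment arm will analyze data". It then says that the principal investigator, who delivers the interventions, is not blinded, "and the participants will not be blinded to the group allocation".
- **Primary outcome and who rates it.** Outcomes: "The main outcome measure is pain intensity, evaluated according to the PI-NRS". The section on assessment and collection of outcomes says that evaluations are made by digital questionnaire, in which "participants will be invited to self-report their level of pain (PI-NRS"; disability, quality of life and adherence are collected in the same way.
- **Model.** Statistical methods: "repeated measures mixed models with participants from the IG as random effect", with group and time as fixed effects.
- **Data held for one arm only.** Description of the developed smartphone app: "adherence will be monitored using a user activation tracking system assessing the frequency and duration of app use".
- **Committee.** The oversight section says that, as the trial progresses, "any necessary corrections will be addressed through decisions made by the entire committee (all authors".
- **Limitations.** Study limitations names the short follow-up, differences in familiarity with technology, and the absence of a cost-effectiveness assessment. It does not name unblinded self-report.

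**The concern.** A reader who sees a single-blind label on a trial with a subjective endpoint will usually assume that the participant or the outcome assessor is masked. Here the participant is the assessor and knows the arm. Masking the analyst guards against choices made during analysis. It does nothing about how a participant who knows that they have the app, or the paper sheet, scores their pain. The target difference is small (0.58 points on a 0 to 10 scale), so a modest difference in reporting between the arms could account for much of it.

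The one form of blinding that is claimed also conflicts with the plan's own model. If the random effect is fitted as written, the analyst has to be told which participants use the app. The choice then exposed is the adjustment for baseline imbalance, for which the Statistical methods section names no covariates and no rule.

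**Working it through.** **1. Blinding, role by role**

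| Role | Knows the arm? | Source |
|---|---|---|
| Participant | Yes | Blinding |
| Investigator delivering the interventions | Yes | Blinding |
| Rater of the primary outcome (the participant) | Yes | Assessment and collection of outcomes, with Blinding |
| Analyst | Stated as no | Blinding |

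The label rests on the last row alone.

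**2. Can the model be fitted blind?** Let y_ij be the outcome of participant i at visit j, with G_i = 1 for the IG and 0 for the control group (CG). As written, the model is

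y_ij = fixed effects (group, time) + G_i·b_i + e_ij.

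G_i multiplies the random effect b_i, so swapping the arm labels gives a different model. An analyst with a file coded A/B must be told which letter receives b_i, and that discloses the arm. The term also implies:

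- IG: variance σ_b² + σ_e², covariance between visits σ_b²;
- CG: variance σ_e², covariance between visits 0, unless a residual covariance structure, which the article does not name, supplies it.

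The three visits of a CG participant (baseline, 4 and 12 weeks) would then be treated as independent. With a symmetric term,

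y_ij = fixed effects (group, time) + b_i + e_ij for all i,

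swapping A and B leaves the fit unchanged apart from the sign of the group contrast, so arm identity is not needed.

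**3. The other two routes to the analyst**

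- *App records.* They exist in the IG only. The article describes them as visible to the therapist and used to monitor engagement; it does not say that they go to the analyst. However, adherence is among the modelled outcomes, part of it is described as an objective exercise frequency, and no source of session counts is given for the CG. Disclosure through this variable is possible but not established.
- *Committee.* The analyst is an author, so the committee includes them. The article does not say that allocations or results by arm are put before it.

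**4. Illustration of what unblinded self-report could do.** The blinding claim has no figure to reproduce. The inputs come from the Sample size section: s₁ = 1.85, s₂ = 1.26, 17 per group, d = 0.58.

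- Pooled variance: (16 × 1.85² + 16 × 1.26²)/32 = 2.505, matching the stated 2.51; SD = √2.505 = 1.58.
- Standard error of the difference: SD × √(2/n) = 0.448 for n = 25 per arm (as randomised) and 0.477 for n = 22 (half of the 44 before the dropout allowance).
- With no true effect and a reporting bias b favouring the app, the rejection rate of a two-sided 5% test is 1 − Φ(1.96 − b/SE) + Φ(−1.96 − b/SE).

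| Assumed bias b (points) | b/0.58 | 25 per arm | 22 per arm |
|---|---|---|---|
| 0 | 0% | 5.0% | 5.0% |
| 0.2 | 34% | 7.3% | 7.0% |
| 0.3 | 52% | 10.3% | 9.6% |
| 0.58 | 100% | 25.4% | 22.9% |
| 1.0 | 172% | 60.8% | 55.4% |

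The values of b are assumptions; the documents give no estimate. Blinding the analyst changes none of these rates.

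**The case against.** The case for the plan is substantial.

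- **Nothing is concealed.** The Blinding section says who is blinded and who is not, and participants cannot be blinded to an app versus a paper sheet. This stands. The fault is a label that suggests more than it delivers and a missing limitation.
- **The random effect may be a drafting slip.** This is plausible, since group and time are specified as fixed effects for the whole trial. It is nevertheless the current text, and as written it contradicts the Blinding section.
- **Differential expectation may be limited.** Both arms receive the educational and training session and daily notifications. That could narrow the bias, and its size is unknown. The table shows sensitivity only and is not an estimate.
- **Detail may sit elsewhere.** Data release rules and coding procedures are commonly left to an analysis plan or full protocol. Their absence from this article is not counted as a fault.

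A reader might go further and infer that the analyst cannot remain blind at all, because app records exist for one arm and the analyst sits on the committee. The documents do not support that. They do not route app logs to the analyst or show arm-level information to the committee. Outcomes come from a questionnaire described without distinction by arm, and the identity-linked database is open to the principal investigator only. A reader might also infer that most analysis choices would be made with the arms known. Mean or median concerns descriptive reporting, and Pearson or Spearman concerns secondary associations; neither alters the primary between-group test. Nor can it be said that participants are given one-sided information, since the survey and consent texts are not shown.

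**Conclusion.** The point holds on two counts. First, single blind here means analyst blind. The self-rated primary outcome is unprotected, and the limitations do not say so. Second, a random effect for IG participants only cannot be fitted by someone who does not know the arms, so the Statistical methods and Blinding sections contradict each other as written. The same wording leaves within-participant correlation in the CG unmodelled by the random effect.

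The app-use data and the all-author committee are risks without a stated safeguard; they do not show that the blind fails. No size can be given for the bias itself. If it were 0.2 to 0.58 points (assumed), with SD 1.58, 25 per arm and no true effect, false-positive rates would be about 7% to 25%. The contradiction and the labelling fault do not depend on that assumption.

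**What to change.** 1. **Statistical methods:** specify a random effect for every participant in both arms, with group coded A/B. The primary model can then be run without arm identity, and within-participant correlation is handled in both arms.
2. **Trial design and Blinding:** state that participants and the investigator are unblinded, that outcomes are participant-reported, and that only the analyst is masked.
3. **Study limitations:** add that the primary outcome is self-reported by participants who know their allocation.

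The cost is a few sentences. Sample size, data collection and visits are unchanged. The downside is that the stated blinding reads less favourably.
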